   3. *Pre-assessment.* Next, pre-assessment is completed by administering the Life Events Checklist (LEC; (Gray, Litz, Hsu, & Lombardo, 2004)), the PTSD Checklist for DSM-5 (PCL-5, Weathers et al, 2013) and items derived from the Service Receipt Inventory (SRI; (Chisholm, Knapp, et al., 2000)).
2. Randomization
   1. Randomization will be carried out by an independent trial unit (at University of New South Wales) Randomization will be performed using computerised software on a 1:1 basis.
3. PM+ Intervention
   1. *Appointments.* CHW who will make contact with participants for treatment to begin. The first PM+ session will be scheduled within a few days and no longer than one week after the baseline assessment. This therapist will plan five consecutive meetings with the participant.
   2. *Additional instrument.* At the start of PM+ and at the beginning of every session the Psychological Outcome Profiles instrument (PSYCHLOPS; (Ashworth, 2004)) will be administered. This instrument, in contrast to above named instruments will be administered by the therapist *to assess and monitor* progress on problems for which the person seeks help.
4. Post intervention assessment
   1. *1-week follow-up.* The post-intervention assessment (WHODAS, GHQ-12, PCL-5) will be scheduled 7 weeks after the pre-intervention assessment (i.e., 1 week after the 5^th^ PM+ session).
   2. *3-month follow up.*  The follow-up assessment - with the same questionnaires plus the life events measure (LEC) and SRI items but without the treatment satisfaction questionnaire - will be scheduled at 3 months after the 5^th^ PM session.

All instruments will be administered by trained research staff blind to the allocation status of the participants. All independent assessors will receive a five day training in administering the instruments, in general interview techniques, and in responding to participant distress, including, as mentioned, psychological first aid.

*Statistical power and sample size*

Since Study Phase 1 is a small exploratory RCT with 40 participants (20 participants per group), that does not aim to detect statistically significant differences in effectiveness, no power calculations have been (or should be) carried out.

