In Study Phase 3 a total number of 346 participants will to be included. Since we are not aware of intervention studies that have been carried out in this population, and we expect the population to be heterogeneous with respect to the types of common health disorders, we aimed for a relatively conservatively estimated 50% reduction in GHQ-12 symptom score in the PM+ group as compared to a 30% reduction in the control group at 3 months after the conclusion of the study. These estimates are in line with the observed effectiveness of an intervention led by lay health counsellors for depressive and anxiety disorders in a landmark study in primary care in India (Patel et al, 2010). This corresponds with an odds ratio of for the PM+ intervention of 2,3. Power calculations suggest a minimum sample size of 133 participants per group (power = 0.95, alpha = 0.05, two-sided). Taking into account an expected 30% attrition at 3 months follow-up, we aim to include a total number of 346 participants (173 in the PM+ group and 173 in the care-as-usual control group).

*Measures*

The measures for use in this study are in Annex 6.

The below matrix gives an overview of the measures used in the RCT in terms of when they will be assessed and what concepts they assess.

| *Concept* | Pre-assessment measures | Post-treatment assessment measures | 3-months post-treatment follow-up assessment measures |
| --- | --- | --- | --- |
| 1. functioning | WHODAS (**screener)** | WHODAS | WHODAS |
| 1. distress | GHQ-12 (**screener** and **primary outcome**) | GHQ-12 | GHQ-12 |
| 1. adverse life events | LEC |  | LEC |
| 1. violence against women | WHO-VAQ |  |  |
| 1. PTSD | PCL-5 | PCL-5 | PCL-5 |
| 1. Cost of care | SRI items |  | SRI items |

1. WHODAS: socio-demographic information and disability

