Of note, in Nairobi, each primary health care facility, and sub-country hospital, employs a Community Health Extension Worker (CHEW), who coordinates referrals from within the community and to ensure patients are followed-up by nurses and/or Community Health Workers (CHWs). The CHEWs from each health facility of the project is working with will be receiving a small additional allowance for their involvement in the research project. Their involvement will be to monitor that referred patients are actually seen when they are referred to the enhanced usual care or to the subcounty office. The CHEW will complete a basic form to monitor the date, time of the appointments and whether they occurred.

Throughout the trial, we will carefully keep track of the types and amount of support received through SRI items (see measures section above).

*PM+ providers and protocol adherence:*

PM+ providers will be female CHWs, who were recommended by the Ministry of Health, based on those that have shown high performance in their regular health work in the communities. After receiving the recommendation, CHWs will be selected based on individual interviews.

PM + providers will meet the following criteria:

- High school diploma (form 4 level of education or above);
- Reasonable proficiency in both Kiswahili and English language – written and verbal;
- 1-year training post-secondary school as CHWs or health related career;
- 2-years and above experience in community work;
- Already working as a CHW within a given geographical area.

PM+ providers will receive 2 weeks of training. In addition, one professional supervisors will be employed for each of the 3 health facility areas. Protocol adherence will be ensured by the supervisors and weekly group supervisions of the CHWs (Murray et al, 2011). Supervisors will then receive their own supervision and on-the-job training in supervision skills by the project lead consultant, who is a qualified counselling psychologist and available for any specific and/or urgent cases where either the CHWs themselves, the supervisors or any of the clients in the program need support. This will take place weekly as well.

To ensure adherence to the PM+ manual and ensure fidelity of interventions, 10% of all PM+ sessions will be attended by the supervisor, using a checklist to ensure basic elements of the PM+ intervention have been followed as required.

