**Data Management and Statistical Analysis**

The data, as collected by the interviewers (Study Phases 2 and 4) and independent assessors and PM+ providers (Study Phases 1 and 3) will be safely stored at the World Vision office of the field coordinator at Rituta ADP

Quantitative data will be coded and the identifying key (a list connecting names to numbers) will be kept in a separate, secure locked location in the field coordinator’s office. The data will be entered into a data-analytic computer program (e.g., SPSS), without the identifying key. Data will only be available to the members of the project group. No attributable data will be used in publications. The investigators will analyze the data, and both positive and negative trial results will be disclosed. Results will be submitted for publication to peer-reviewed scientific journals.

The qualitative research will follow thematic analyses as described above.

For the RCT’s, both intention-to-treat analysis and completers’ analyses will be carried out. To measure comparisons at baseline between the two treatment groups t-tests will be conducted for continuous variables and chi-squared test for categorical ones. Repeated measurement analysis will be carried out to assess differential change over time in mean GHQ-12 scores between groups. We will add the following covariates at baseline to examine subgroup effects: education, employment, and severity of symptoms. All analyses will be carried out in SPSS, with p-levels of <.05 indicating statistical significance.

For the economic evaluation, we follow the approach used before in a similar trial (Buttorff et al, 2012). The number of days with reduced working hours because of poor health will be calculated from the WHODAS-12. Participants’ self-reported their health-care utilization, medication use and out-of-pocket payments will be measured with the items derived from the SRI at post treatment and 3 months follow-up.

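### PM+ women are nested within the CHW who treats them, but neither the sample size nor the stated analysis allows for it; the likely effect is modest and depends on a CHW count and ICC the protocol does not give.

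*Protocol*

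**What the plan says.** **Delivery.** Under PM+ providers and protocol adherence: "PM+ providers will be female CHWs, who were recommended by the Ministry of Health". They are then chosen by interview, trained for two weeks and supervised weekly in groups, with one supervisor for each of three facility areas. Under Procedure (PM+ Intervention, Appointments), after the CHW makes contact: "This therapist will plan five consecutive meetings with the participant". Under Enhanced Treatment-as-usual, control women are referred to primary care clinicians, usually nurses. The protocol does not say how many CHWs deliver PM+ or how many women each one treats.

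**Allocation.** "Randomization will be performed using computerised software on a 1:1 basis". No cluster unit is named.

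**Sample size.** Under Statistical power and sample size, the effect is a "50% reduction in GHQ-12 symptom score in the PM+ group as compared to a 30% reduction in the control group", followed by "This corresponds with an odds ratio of for the PM+ intervention of 2,3" and "Power calculations suggest a minimum sample size of 133 participants per group (power = 0.95, alpha = 0.05, two-sided". Then: "Taking into account an expected 30% attrition at 3 months follow-up, we aim to include a total number of 346 participants". Attrition is the only inflation applied.

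**Analysis.** Under Data Management and Statistical Analysis: "Repeated measurement analysis will be carried out to assess differential change over time in mean GHQ-12 scores between groups". The covariates named are education, employment and symptom severity. CHW, supervisor, facility and area do not appear.

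**The concern.** Women are randomised individually, but once allocated to PM+ a woman's outcome may depend on which CHW treats her. Women sharing a CHW then have positively correlated outcomes, and the PM+ mean has a larger variance than 173 independent women would give. The control arm has no matching CHW structure, so the extra variance falls on one side of the comparison.

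A sample size and an error term that assume independent women leave this component out. The error runs in the anti-conservative direction: intervals too narrow, power too high. It matters here because the trial is meant to support scaling up delivery by lay workers (Rationale; Expected Outcomes). Differences between those workers are part of the uncertainty about what a wider programme would achieve.

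**Working it through.** **1. The plan's own figure.** The odds ratio shows that 50% and 30% were used as proportions: (0.5/0.5)/(0.3/0.7) = 2.33. The standard two-proportion formula, two-sided alpha 0.05 and power 0.95, gives

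n = [1.960·√(2·0.4·0.6) + 1.645·√(0.25 + 0.21)]² / 0.2² = 153 per arm,

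or 163 with continuity correction. The stated 133 does not reproduce. The 173 is 133 × 1.3 = 172.9; dividing by 0.7 would give 190. At 30% attrition, 173 leaves 173 × 0.7 = 121 completers per arm. With independent women, power for 50% against 30% is 0.919 at 133 per arm and **0.893** at 121. All of these formulas assume independence.

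**2. What the documents imply about CHW numbers.**
- Upper bound (Overview): 3 facilities × up to 100 CHWs × under 50% staffing gives fewer than about 150. At that extreme there would be 173/150 ≈ 1.2 PM+ women per CHW.
- Screening (Procedure, Selection): 3460 women, one per household, from lists of 100 households per CHW, gives 3460/100 = 34.6, so at least 35 lists. If each woman is treated by her own area's CHW (not stated), about 35 providers is a natural case.
- Fewer is possible, because providers are a selected subset, and 173 × 5 = 865 sessions must be supervised by three people who attend 10% of them.

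I therefore show 35, 20 and 10 CHWs. Both these counts and the ICC of 0.02-0.05 are assumptions.

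**3. Formulas.** With k CHWs, m = 121/k women each and intraclass correlation ρ:
- design effect in the PM+ arm only: D = 1 + (m − 1)ρ
- variance inflation of the difference, taking equal arm variances: V = (1 + D)/2
- unadjusted type I error: 2[1 − Φ(1.96/√V)]
- power: the two-proportion calculation at 121/V per arm
- relative narrowing of the unadjusted interval: 1 − 1/√V

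Example, k = 20 and ρ = 0.05: m = 6.05, D = 1 + 5.05 × 0.05 = 1.2525, V = 1.126, √V = 1.061. Type I error is 6.5%, power at 121/1.126 = 107 per arm is 0.854, and the interval is 1 − 1/1.061 = 5.8% too narrow.

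**4. Results.**

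| CHWs | m | ρ | V | Type I error | Power | CI too narrow by |
|---|---|---|---|---|---|---|
| 35 | 3.5 | 0.02 | 1.025 | 5.3% | 0.885 | 1.2% |
| 35 | 3.5 | 0.05 | 1.061 | 5.7% | 0.874 | 2.9% |
| 20 | 6.05 | 0.02 | 1.050 | 5.6% | 0.878 | 2.4% |
| 20 | 6.05 | 0.05 | 1.126 | 6.5% | 0.854 | 5.8% |
| 10 | 12.1 | 0.02 | 1.111 | 6.3% | 0.859 | 5.1% |
| 10 | 12.1 | 0.05 | 1.278 | 8.3% | 0.807 | 11.5% |

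At m = 1, D = 1 and nothing changes. An ICC of 0.10 with 10 CHWs would give power of about 0.73 and type I error of 11.6%; that is an unfavourable corner, not a central case.

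**The case against.** **Caseload is not stated.** A reader might infer that the protocol has each CHW treating several PM+ women. It does not say so, and the upper bound on the CHW pool would allow close to one each. This stands. Selection, two weeks of training per provider and three supervisors make a caseload above one very likely, but it remains an inference.

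**The analysis detail may sit in an SAP.** Provider terms and df corrections are often specified there, and none is at hand. This weakens the analysis half of the point. It does not touch the sample size, which the protocol fixes.

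**Type I error need not exceed 5%.** A reader might conclude that the test is simply invalid. With individual randomisation, if PM+ changes no woman's outcome, her CHW cannot induce correlation through treatment and the test keeps its level. Inflation arises only if provider effects vary around a zero mean and the inference is to CHWs in general. For these particular CHWs, treating them as fixed is defensible. The objection stands as a condition on the point; the stated aim of scale-up argues for the wider inference.

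**Clustering does not explain the missing power.** The step from 0.95 to 0.893 comes from 133 not reproducing and from attrition applied as ×1.3. This stands too. In addition, 0.893 is for two proportions, whereas the planned analysis compares mean GHQ-12 and no SD is given.

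**A design effect on all 346 women** is another tempting reading. It would overcorrect, because TAU women are not nested in CHWs. Clustering by nurse in TAU is possible, but nothing in the protocol allows it to be sized.

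**Conclusion.** The point holds in a limited form. PM+ delivery is nested within CHWs in one arm only, and the sample size and the analysis as stated ignore this. With more than one woman per CHW and CHWs who differ in effect, the standard error for generalising to CHWs is too small and power is overstated.

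The size is small to moderate. Against an unclustered 0.893, the loss is about 1 to 2 percentage points of power with 35 CHWs, 2 to 4 with 20 and 3 to 9 with 10, at the assumed ICCs. These figures rest on equal caseloads, a normal approximation without df correction, and the plan's 50% against 30%. They show direction and order of magnitude, not the power of the GHQ-12 mean comparison. They do not show that the trial is underpowered because of clustering or that its conclusions would be unsound.

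**What to change.** 1. Record the delivering CHW for every PM+ woman as a data field. CHW session records are already reviewed under process monitoring, so the link probably exists and needs only to reach the analysis file.
2. Fit the primary model with a CHW random effect in the PM+ arm only (a partially nested mixed model), with a small-sample df correction because there may be few CHWs.
3. Restate the power for 346 with the actual number of CHWs and a range of ICCs, on the scale of the planned analysis. Enrolment does not change.

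The cost is one data field, one model term and a rewritten power paragraph. The downside is a slightly wider confidence interval and a lower stated power.

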**Study Phase 2 and 4: Process evaluation of administering PM+ in Nairobi, Kenya**

The feasibility, and difficulties and successes in carrying out research and intervention activities will be explored through comprehensive process monitoring (see step 1 below) and semi-structured interviews with 20 KIs, including 5 CHWs (See step 2 below). Burden of completing the assessments and PM+ on the time and effort of participants, satisfaction with the intervention, and barriers and facilitators to adherence will be explored through semi-structured interviews with a sample of 5 participants (including participants that have dropped out). In addition, 5 decision-makers with responsibilities for developing or implementing health policy, including heads of the relevant clinics, and 5 PHC staff (clinical officers/nurses) will be interviewed to obtain their perceptions of the benefits and challenges of integrating PM+ into the CHWs routine service provision.

*Step 1. Process monitoring*

Process monitoring includes review of CHW records of sessions with clients; supervision records including intervention fidelity monitoring; and supervision of supervisors by intervention trainers. This data will be collected throughout the intervention delivery and reviewed as it is collected, leading to an iterative process of intervention monitoring informing intervention delivery. Confidential case notes and information will be handed to the research site for secure filing.

*Step 2: semi-structured interviews*

As mentioned above, additional individual semi-structured interviews will be conducted with 5 participants from each category of: intervention recipients; CHWs; clinical staff; and local stakeholders with a role in policy development or implementation. The aim of these interviews are to (a) make any necessary adjustments to the trial design (for KIs done after the exploratory RCT) and (b) explore the feasibility of wider implementation of the intervention in the Nairobi counties (for KIs done after the definitive RCT).Interviews will follow a semi-structured interview guide. A draft semi-structured interview guide has been developed (see Annex 5) with key questions that are identified for exploration, with additional prompt questions to fully explore each question in depth.

Interviews will follow the same process as outlined for Phase 1. Namely: informed consent will be obtained using the same informed consent procedure as in Phase 1 and 3 from all participants immediately prior to interviews (see KI consent form in annex 4); all interviews will be conducted by a pair of trained interviewers, one of whom will ask the questions and the other will record responses. No identifying information will be collected during the interview, with all data anonymised; and no recording devices will be used. Interviews will be conducted no longer than 4 weeks after the conduct of final outcome assessments, and are expected to last no longer than one hour. All key informant data will be analysed following thematic analysis

**Safety Considerations**

The World Vision Kenya team – which is very familiar with this subcounty – has confirmed, that CHWS and independent assessors can safely work in this community, including at people’s homes..

During the entire study, participants both in the PM+ or TAU arms will have access to enhanced usual care provided by trained primary care clinicians in the study area. If during the course of treatment, participants present with urgent psychiatric problems requiring referral to a specialist (e.g., a psychiatrist) or follow-up, this will be arranged with the CHW and health facility staff. Individuals will be referred to the to the Mbagathi sub county hospital.

Participants may experience benefits from the intervention that may be difficult for other family members to relate to. However, by carrying out community consultations before the project and in study phase 1 to ensure that PM+ is culturally acceptable, we expect that the intervention will not lead to behavior changes that are unacceptable within the local culture. In particular it should be noted that the intervention includes a focus on strengthening social supports in the participant’s lives. Participants with recently developed, acute protection risks will be offered psychological first aid by the PM+ provider (WHO, War Trauma Foundation and World Vision International, 2011) and linked to available support services/resources. So PM+ providers will have been trained to address this.

Information safety issues of the research staff and PM+ providers will be overseen by the Office of Corporate Security Team of World Vision Kenya, operating in their Nairobi HQ and providing security briefs to all World Vision Kenyan offices regarding security risks that may be imminent in certain areas. World Vision Kenya will not permit study members to engage in community work on days where insecurity is a risk. Therefore, all staff involved in the study have been advised that their wellbeing and safety come first and foremost, and that they are to end their work immediately if they become unsafe.

Safety of assessors will be ensured by the fact that assessors will be working in groups, dropped to particular areas each day and meeting up as specific times throughout their days. Thus, they will work in close proximity to each other and provide support and protection for each other.

The CHWs, who will provide the PM+ intervention, already visit specific households as a standard part of their work with health facilities in the area. A local security assessment has indicated that it will be safe for screeners, assessors and CHWs to work at the household level.

All assessors and PM+ providers will receive pre-paid phone credit by the project to facilitate constant communications with each other and with the local World Vision office.

At the end of the study (at 4-5 months after inclusion), participants in the TAU condition will also be offered the PM+ intervention, if still indicated. If after the project, participants continue to experience psychological problems they will be offered additional support through aforementioned referral hospital, see above).

All adverse reactions and serious adverse events (SAEs) reported spontaneously by the subject or observed by the investigators or other staff members will be recorded by the research team. We consider an event a SAE if it is an undesirable experience occurring to a subject during the study, whether or not considered related to the research procedure. Although it is unlikely that SAEs would occur given the nature of the intervention, all adverse events and SAEs will be reported to the local independent advisory board.

The local advisory board will consist of: an independent medical officer (chair), an independent counselling psychologist with community mental health experience, the site principle investigator, and the clinical supervisor. All serious adverse events (SAE) and adverse events (AE) will be reported by the local principle investigators or supervisor to this advisory board. The chair or a nominated person from the advisory board will review SAEs within 48 hours.

Terms of reference of the advisory board are . 1. to establish rules and procedures governing its own meetings, consistent with the research protocols and standard; 2. to review SAEs within 48 hours, and all (S)AEs once a month and determine whether an (S)AE is likely to be related or unrelated to the intervention. 3 as necessary, recommend appropriate action in respect of ongoing trial conduct (such as referral to specialized care or installing extra assessment points for monitoring participants), and 4. follow-up to know whether recommended actions have taken place

On the informed consent form, patient information is included to inform participants that the field coordinator, or another clinician other than their therapist are available to them if they are upset by this study.

The principal investigator will inform the subjects and the WHO ERC if anything occurs, on the basis of which it appears that the disadvantages of participation may be significantly greater than was foreseen in the research proposal.

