Twenty female independent assessors will be recruited. All 20 will be involved in the screening and in the pre and post assessments. A pool of candidates fitting the assessor criteria will be identified, with final selection of assessor made by the World Vision Field coordinator and World Vision Kenya site PI who has no personal knowledge of the candidates. Selection will be based upon fit to the assessor criteria, qualifications and skills and availability for the study timeline. During the recruitment process, assessors will be told interviewers about the potential stressful nature of the job. All assessor will receive a 5-day training on interview techniques, screening and assessment instruments and psychological first aid. A 1-day refresher training will be delivered by the investigators following the “just in time” training principle whereby training is delivered immediately prior to the conduct of interviews. During the project, the interviewers will also get support and supervision by the supervisor to handle possible difficulties they might experience

**Study Phase 1: Exploratory (Pilot) RCT to evaluate feasibility of administering the local adaptation of PM+ in a RCT setting and Study Phase 3: Definitive RCT to evaluate effectiveness and cost-effectiveness of the local adaptation of PM+ for use in Nairobi, Kenya**

Below we provide an overview of the design and methods of Study Phases 1 and 3. Note that the planned design and measures of Study Phase 1 and 3 are identical except for (a) the sample size and (b) the exploratory RCT does not involve a 3 months assessment follow-up. Study Phase 1 is an exploratory RCT that precedes the definitive RCT, and is intended to test the feasibility and acceptability of testing the PM+ intervention in a large RCT in Kenya, thereby testing the study procedures in the setting in which Study Phase 3 will be conducted.

*Overview*

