**Follow-Up**

The exploratory RCT and definitive RCT differ in follow-up assessments. While in the exploratory RCT, the final post intervention assessment by independent assessors is 1 week after the completion of PM+, in the definitive RCT the final outcome measures will be taken at 3 months after the final PM+ session. As mentioned, 5 participants will also be invited to participate in semi-structured interviews. These interviews will be conducted within 4 weeks of the final outcome assessment (i.e within 4 months of the intervention). All participants will be told that they may contact their local primary health care facility in case they need future support. Names and contact details of the field coordinator and local site PI will be provided on the consent form of which all participants receive a copy.

Depending on the adverse event, follow up may require additional tests or medical procedures as indicated, and/or referral to the general physician or a medical specialist. All adverse events will be followed until specialist care (including referrals, additional tests or medical procedures) is in place for the client, or until a stable situation has been reached.

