**Duration of the Project**

|  | |
| --- | --- |
| **Study Phase 1: Exploratory randomised controlled trial** | |
| **Activities** | **Month** |
| Selection and training of CHWs (PM+ providers) and their supervisors and independent assessors | February 2014 |
| Participants are identified | March 2014 |
| Pre-intervention data are collected | April 2014 |
| CHWs (PM+ providers) implement PM+ | May-July 2014 |
| Post intervention data is collected from service users and control group | August 2014 |
|  |  |
| Control group participants who have not shown improvements are referred for PM+ | August 2014 |
| Data entry | August-Sept 2014 |
| Analysis and report of exploratory RCT results | October-Nov 2014 |
| **Study Phase 2: Process evaluation of exploratory RCT** | |
| **Activities** |  |
| Process monitoring | September 2014 |
| Qualitative interviews | September 2014 |
| **Study Phase 3: Definitive randomised controlled trial** | |
| **Activities** | **Month** |
| Pre-intervention data are collected | December 2014 |
| CHWs (PM+ providers) implement PM+ | Jan-May 2015 |
| Post intervention data is collected from service users and control group | June 2015 |
| month follow up data is collected | August 2015 |
| Control group participants who have not shown improvements are referred for PM+ | July 2015 |
| Data entry | Dec 2014 – August 2015 |
| Analysis and preparation of manuscript describing effectiveness and cost-effectiveness of PM+ in Nairobi, Kenya | August-Sept 2015 |
|  |  |
| **Study Phase 4: Process evaluation of definitive RCT** | |
| **Activities** |  |
| Process monitoring | August 2015 |
| Qualitative interviews | August 2015 |

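### The phase 3 timetable refers unimproved TAU women to PM+ in July 2015, before the August 2015 visit that supplies the primary outcome

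*Protocol*

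**What the plan says.** Two parts of the protocol fix when control women may receive the trial intervention.

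- **Safety Considerations:** "At the end of the study (at 4-5 months after inclusion), participants in the TAU condition will also be offered the PM+ intervention", provided it is still indicated.
- **Duration of the Project, Study Phase 3:** "Control group participants who have not shown improvements are referred for PM+ | July 2015".

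The neighbouring phase 3 rows are "CHWs (PM+ providers) implement PM+ | Jan-May 2015", "Post intervention data is collected from service users and control group | June 2015" and "month follow up data is collected | August 2015". The digit before the word month is missing from the last row, but the Measures matrix and Follow-Up make clear that it is the 3-month visit.

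That visit carries the primary outcome. The GHQ-12 paragraph under Measures defines it as distress 3 months after the fifth session, and Follow-Up states that "in the definitive RCT the final outcome measures will be taken at 3 months after the final PM+ session".

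Phase 1 has no such ordering. Its row reads "Control group participants who have not shown improvements are referred for PM+ | August 2014", the same month as its last assessment, and "the exploratory RCT does not involve a 3 months assessment follow-up".

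**The concern.** The text and the timetable give different orders for two events whose order matters. Under the text, controls are offered PM+ when the study ends. Under the timetable, they are referred one calendar month before the primary outcome is collected.

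The timetable limits referral to controls who have not improved. Early crossover would therefore tend to improve the worst outcomes in the TAU arm and pull that arm towards PM+. The planned intention-to-treat comparison (Data Management and Statistical Analysis) would then understate the effect of PM+. Outcomes measured after such exposure could not be cleanly repaired in the analysis.

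**Working it through.** **1. The participant clock.** Under Procedure, the post-assessment is 7 weeks after the pre-assessment and 1 week after the fifth session. The fifth session is therefore at 7 − 1 = 6 weeks. The primary visit is at 6 weeks + 3 months ≈ 19 weeks ≈ 4.4 months. This agrees with the 4-5 months in Safety Considerations, so that text is consistent with an offer after the visit. It does not guarantee one, because the window opens at 4.0 months and is not tied to the visit.

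**2. The project calendar.** Delivery runs January to May 2015, and May + 3 months = August 2015. The August follow-up row is thus correct for women in the last delivery month, and July is the date out of line.

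**3. Who is exposed.** The timetable puts baseline in December 2014. On the participant clock:

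- 1 December + 6 weeks = 12 January; + 3 months = 12 April 2015
- 31 December + 6 weeks = 11 February; + 3 months = 11 May 2015

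Women who keep to that clock are measured well before July. The conflict concerns women followed up in August as the timetable schedules, which corresponds to fifth sessions in May.

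**4. How much PM+ fits in the gap.** From a July referral to an August visit is 1 day (31 July to 1 August) to 61 days (1 July to 31 August). At six weeks to the fifth session, referrals on 1, 15 and 31 July would finish on 12 August, 26 August and 11 September. Exposure by the visit therefore ranges from none to all five sessions. If both dates are spread evenly over their months, the mean gap is 31 days, and 210 of 961 date pairs (22%) leave 42 days or more.

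**5. Effect on power (illustrative).** The protocol gives neither uptake nor benefit by the visit, so both are assumed. Let s be the share of TAU women who start PM+ early and f the fraction of its benefit they have by the visit. The contrast shrinks to d × (1 − s × f).

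The planned 95% power at 133 per group (two-sided alpha 0.05), solved for a two-sample t-test, gives d = 0.444. After the expected 30% attrition, 173 × 0.7 ≈ 121 per arm remain, with 93% power at that d.

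| Benefit by visit (f) | 133 per arm: s = 10 / 20 / 30% | 121 per arm: s = 10 / 20 / 30% |
|---|---|---|
| none | 95% | 93% |
| 0.25 | 94 / 93 / 92% | 92 / 90 / 89% |
| 0.5 | 93 / 90 / 87% | 90 / 87 / 83% |
| 1 (upper bound) | 90 / 82 / 71% | 87 / 79 / 67% |

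The contrast shrinks by 0.1 × 0.25 = 2.5% at the least and 0.3 × 1 = 30% at the most.

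**6. Sensitivity to the baseline.** The d above is back-solved from the stated power. If the planned 50% and 30% are read as responder proportions (odds ratio (0.5/0.5)/(0.3/0.7) = 2.33), power is 92% at 133 per arm and 89% at 121 with no crossover. At 133 per arm it falls to 89 / 85 / 81% with f = 0.5 and to 85 / 76 / 64% with f = 1. The starting level changes; the direction does not.

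**The case against.** The best defence is that the operative text already has the order right and the timetable is only a coarse calendar. Safety Considerations tie the offer to the end of the study, and Follow-Up makes the 3-month visit the final measurement. The calendar cannot be read literally for each woman: a December baseline on the Procedure schedule puts every 3-month visit before mid-May, so the June and August rows do not fit that schedule either. The July row is also printed below the August row, which suggests a simple date slip. Finally, any contamination would bias towards no effect and could not create a false positive.

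Much of this stands. A slip is quite possible, women on the December clock are unaffected, and the full-benefit column is a ceiling: with evenly spread dates, only about 22% of date pairs allow all five sessions before the visit.

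It does not remove the conflict. Staff could reasonably work from the timetable, nothing in the document corrects July, and no sentence makes referral wait for a woman's own visit. The 4-5 month window would permit an offer at 4.0 months, ahead of a visit at about 4.4. Women with fifth sessions in May and visits in August remain exposed. Bias towards no effect still matters in a trial meant to settle whether PM+ works.

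**Conclusion.** The concern holds: the protocol is wrong as written on this point. The contradiction between the text and the phase 3 timetable is certain. The harm is conditional on the July date being followed, on how many unimproved controls take up PM+, and on how much they benefit before the visit.

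At 133 per arm with 10% to 20% uptake and a quarter to half of the benefit, the loss is 1 to 5 percentage points of power. Larger losses need high uptake and nearly complete treatment by the visit. The figures assume a constant effect and a test at a single time point; the protocol plans a repeated-measures analysis, so absolute power may differ. The point should be corrected before phase 3 starts; confidence that it would cause real damage is moderate.

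**What to change.** 1. In the phase 3 timetable, move the control referral to after the August 2015 follow-up, for example to September 2015.
2. In Safety Considerations and in the timetable, state that no TAU woman is offered or referred for PM+ until her own 3-month assessment is completed or its window has closed. Leave the urgent referral route for severe disorders and suicidality unchanged.

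The cost is one date and one sentence, submitted to the two ethics bodies named under Ethics. Unimproved TAU women would wait about one to two months longer than the July date, with enhanced usual care and urgent referral still open to them. Even at the trial arm's five-month delivery pace, a September 2015 start would finish in January 2016, within two years of the February 2014 start.
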